**Fig. 2 Fig2:**
[figure not shown]
Schematic overview of intervention study

**Fig. 3 Fig3:**
[figure not shown]
Intervention timescale

The randomised crossover design was chosen because blinding of the control group is not possible and thus contamination effects are to be expected. Because of the big differences between the participating clinics with regard to organisational structures, and therefore the expected differences in the outcomes, cluster randomisation is not possible.

The survey will focus on psychosocial factors related to parent satisfaction and psychosocial distress (primary outcome) and possible effects on visit frequency, breastfeeding behaviour and breast milk production (secondary outcome). In addition to the quantitative analysis of the parents’ survey outcomes, there will be an analysis of the log-in data from the webcam portal. By linking these data with the survey data, the different usage behaviours can be descriptively explored, and possible connections to the outcomes can be derived. In the second year of the evaluation, all intervention groups will receive the practical guidance. Data will be managed by the Institute of Medical Sociology, Health Services Research and Rehabilitation Science (IMVR). The pseudonymised data is administered by a data manager who operates technically and organisationally separated from the evaluating scientists. The primary outcome will be analysed after completion of data collection, no interim analyses are planned. All adverse events caused by the camera system will be collected and reported.

Sample size calculation was derived from case numbers of premature neonates with a birth weight below 1500 g of each participating clinic. There has been no power calculation since this study will follow an exploratory approach and generate first effect-size estimators, which can be the basis of the case number estimation for a possible follow-up study. Cross-over effects as well as carry-over effects and period effects will be calculated. For all effects 95% confidence intervals will be given. Since all analyses are of exploratory nature, no adjustment for multiple testing will be made.

### Work package 6

Dealing with data protection law. Basic legal issues regarding data protection, as well as relevant special legal issues regarding data protection (e.g. for workplace monitoring) will be analysed in detail for the use of webcams in neonatal intensive care units. Here, video surveillance, which is generally a relevant data protection process [23], will take place in a particularly sensitive environment that needs a high degree of protection [24]. In addition to the monitored newborns, parents and third parties – such as nurses, doctors and visitors – might also be seen through the camera. Therefore, the legally compliant use of webcams requires the consent of the data subject, or a legal basis for the surveillance (see Art. 6 General Data Protection Regulation (GDPR)). Difficulties in defining the legal basis arise since, in law, data processing in the context of employment (Art. 88 GDPR) has different requirements from data processing outside this particular situation (Art. 6 et seq. GDPR). In the health sector, additional special requirements must be fulfilled (Art. 9 GDPR). However, it is not only the GDPR (the main relevant European data protection framework) that must be taken into account, as national regulations such as the Health Data Protection Act of North Rhine–Westphalia (GDSG NRW) or the Hospital Act of North Rhine–Westphalia (KHG NRW) can also apply. In any case, there is no specific legal basis for the use of video surveillance in hospitals [25]. Therefore, all these legal requirements will be addressed in the study.

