## Background

Postnatal care for newborns with special care needs is provided in neonatal intensive care units (NICUs). Newborns with special care needs are usually premature babies, or babies born on time with congenital malformations or complications resulting from childbirth or pregnancy. Premature infants, who make up the majority of the patients cared for in NICUs [1], and very small babies with a birth weight below 1500 g or with a gestational age below the 32nd + 0 week, in particular, often need long-term care in a NICU [2].

During their stay in the NICU, the patients are separated from their parents most of the time. This separation, especially from the mother, can have far-reaching consequences for the mother [3], and a great impact on the bond between the parents and the child [4]. The separation of a mother and her child can impede the development of maternal feelings [5] and decrease the mother’s sense of responsibility and sensitivity [6]. At this time, when role structures are changing, the relationship between fathers and children is playing an increasingly important role. It has been shown that more and more fathers of premature babies are suffering from depression and anxiety [7]. Such psychological strains, which may manifest over the long term, can in turn have an impact on the development of the preterm infant [8]. Furthermore, it has been shown that unrestricted visiting hours and developmentally supportive care can foster parental satisfaction [9]. One way to counter the consequences of the spatial separation between newborns and their parents is to set up webcams in NICUs. Through a webcam installed by the newborn’s bed, parents and other family members can keep in touch with the baby when they are not on site. There are expected to be indirect effects on the medical outcomes for the newborn through, for example, the increased well-being of the parents [10]. The strengthened feeling of being close to the child is understood to promote lactation and thus to foster the nutrition of the newborn with breast milk [11]. In addition to the positive effects of webcams, however, a few parents also report increased fears, triggered by the observation of critical situations as well as by the difficulty of estimating the child’s condition from afar [12].

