The evaluation of the use of webcams will be based on the Medical Research Council (MRC) framework for the evaluation of complex interventions [22]. The intervention is to be regarded as complex according to the MRC framework, as a variety of outcomes have to be considered and different parties will be affected by the intervention, which will take place in a complex organisational setting. The evaluation of this complex intervention will be carried out as part of a randomised cross-over design trial using a waiting-list control group design. The evaluation of the outcomes (summative, ex-post) will be accompanied by a process evaluation (formative, ongoing).  A schematic overview of intervention study can be found in Fig. 2. In four cooperating NICUs (University Hospital Cologne, University Hospital Bonn, University Hospital Düsseldorf, Marienhaus Klinikum St. Elisabeth Neuwied) all parents with a premature baby below 1500 g (*n* = 730) will be invited to take part in the study by the treating neonatologist. Parental consent will be obtained for participation in the study. If the parents refuse to participate in the study, they will be asked to fill out a short questionnaire, which will inquire about the possible reasons for refusal. After the participating parents have been included in the study they will be randomly allocated to the control group or the intervention group by pre-prepared study documents, which randomise the participants to the different points in time of the intervention. Allocation to the control or intervention group is based on a pre computer generated randomisation list for each NICU created by a statistician. Allocation concealment will be guaranteed by opaque, sealed envelopes. After a month, the control group will change with the intervention group. Thus, both groups will receive the intervention, but with a time delay of 4 weeks. The first group will receive the camera in the first 4 weeks of the study period, whereas the second group will receive the camera in the last 4 weeks of the study period. The intervention timescale is presented in Fig. 3.

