## Discussion

To our knowledge, this is the first study that comprehensively accompanies and evaluates the use of webcams on multiple NICUs, with regard to parental outcomes and effects on the medical staff. There are already international studies on the use of webcams on NICUs on the topics of additional workload of the nursing staff [13], attitudes towards the cameras of parents, doctors and nursing staff [14, 26], camera usage behaviour [27] and effects of the camera on the length of stay of the premature baby [28]. However, this study examines for the first time primary and secondary outcomes of parents with respect to camera use using validated scales that allow a direct comparison between intervention and control groups. Furthermore, this study benefits from its high number of cases targeted and the evaluation of effects on both parents and physicians as well as nursing staff. In addition, the compilation of practical guidance in the second year provides the opportunity to counteract preconceptions on the parents’ side concerning the camera use and to inform properly about the camera system.

It should be noted, however, that this study is not a clinical study but a health services research study and therefore evaluates the effectiveness not the efficacy. Methodologically, this results in some limitations of the study. A blinding of the intervention and control group is not possible, since the use of the camera is an obvious intervention which cannot be blinded from any of the persons involved. Furthermore, the measured outcomes are mainly patient reported outcomes reported through questionnaires.

Yet this study can be regarded as a pragmatic trial providing necessary evidence to decide whether to promote the use of webcams on NICUs or not and what to consider when implementing them.

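### Adverse events are collected by unblinded attribution to the camera, so their counts cannot show excess harm between camera and no-camera periods

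*Protocol article*

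**What the plan says.** Work package 5 of the protocol article has a single sentence on safety: "All adverse events caused by the camera system will be collected and reported". It does not say who decides that an event was caused by the camera or on what criteria, and it does not mention recording events irrespective of cause.

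The evaluation is a "randomised cross-over design trial using a waiting-list control group design". On timing, "The first group will receive the camera in the first 4 weeks of the study period", and the other group has it in the last 4. Every family thus contributes one camera and one no-camera period. The Discussion states that "the use of the camera is an obvious intervention which cannot be blinded from any of the persons involved".

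Two other statements bear on harm. The Background notes that with webcams "a few parents also report increased fears, triggered by the observation of critical situations". Work package 5 makes psychosocial distress part of the primary outcome, and the Discussion describes the outcome measures as "validated scales that allow a direct comparison between intervention and control groups".

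**The concern.** The rule selects events on judged cause before they are recorded, and everyone in a position to judge knows whether a camera was running. What reaches the record then depends on how readily parents and staff blame the camera as well as on how often events occur. A harmless camera can collect events through over-attribution. A harmful one can look clean if the harm is indirect and nobody links it to the camera.

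The randomised no-camera period would remove the need for case-by-case attribution, but the rule as written does not use it for events. A later analysis plan cannot repair this, because it cannot recover events that were never collected. The Discussion says the trial should inform whether webcams are promoted, so a reader may look to the event list for a statement on safety that it cannot give.

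**Working it through.** **No figure to reproduce.** The article states no adverse-event rate, no safety sample size and no power. The 730 is the number of premature babies whose parents will be invited, and it comes from clinic case numbers.

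**The rule set against the exposure pattern (Work package 5).**

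| Group and period | Camera | When an event enters the record |
|---|---|---|
| First group, first 4 weeks | yes | if attributed to the camera |
| First group, last 4 weeks | no | only if traced to earlier camera use |
| Second group, first 4 weeks | no | only through contamination from other families' cameras |
| Second group, last 4 weeks | yes | if attributed to the camera |

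The second row is not strictly empty, because the plan itself allows for delayed effects: "Cross-over effects as well as carry-over effects and period effects will be calculated". The third row is empty apart from contamination, which Work package 5 expects. In neither no-camera row does the recorded count follow the background rate.

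**What the counts estimate.** Let N be the number of families completing both periods, b0 and b1 the event probability per 4-week period without and with the camera, and a the share of camera-period events attributed to the camera.

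- Quantity wanted: N × (b1 − b0).
- Recording regardless of cause: N × b1 against N × b0, whose difference is the quantity wanted.
- Stated rule: N × b1 × a against about 0, so the difference is about N × b1 × a.

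The last expression does not contain b0. It equals the quantity wanted only if a = (b1 − b0)/b1, that is, only if unblinded attribution is exactly right on average. With no true effect this requires a = 0.

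**Illustration with no true effect (b0 = b1 = b).** N = 730 is an upper bound, since it assumes all invited families take part and complete both periods. The values of b and a are assumptions.

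| b | Recorded regardless of cause, each condition: 730 × b | Stated rule, camera, a = 5% to 20%: 730 × b × a | Stated rule, no camera |
|---|---|---|---|
| 2% | 14.6 | 0.73 to 2.92 | about 0 |
| 5% | 36.5 | 1.83 to 7.30 | about 0 |
| 10% | 73.0 | 3.65 to 14.60 | about 0 |

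**The same record fits different truths.** A count of 7.3 arises from b = 5% with a = 20% (730 × 0.05 × 0.20) and from b = 10% with a = 10% (730 × 0.10 × 0.10). If the camera raised the rate from 5% to 10%, the true excess would be 730 × (0.10 − 0.05) = 36.5 events. With a = 5% the record would show 730 × 0.10 × 0.05 = 3.65, fewer than the 7.3 shown for a harmless camera at b = 5% and a = 20%.

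**The case against.** Several stronger readings are tempting, and the documents do not support them.

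- **That harm as a whole cannot be compared.** A reader might infer this, but it is wrong. The harm the Background anticipates is parental fear, which falls within psychosocial distress. That is part of the primary outcome and is compared between conditions whatever anyone attributes to the camera.
- **That no-camera periods have zero events by definition.** This goes too far. The first group's second period follows camera use, and contamination is expected. About zero is the accurate statement.
- **That the plan breaks its promise of 95% intervals.** That promise directly follows the sentence on cross-over, carry-over and period effects and most naturally refers to those. No interval for adverse events is promised, and no comparative adverse-event table is planned.
- **That other events will certainly go unrecorded.** The sentence does not say so. The article condenses a fuller protocol that may define event capture and attribution more closely.

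Beyond these, the trial team can say that listing device-caused events is a coherent and proportionate choice for an exploratory health services study of a bedside webcam. That stands. It limits the importance of the point and rules out calling the plan contradictory.

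What survives is narrower. The published rule makes cause the condition for collection, the judgement of cause is unblinded, and counts so obtained cannot support a statement about excess events. Work package 3 does not fill the gap, because its nursing observations are split before and after the practical guidance, not between camera and no camera.

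**Conclusion.** The point holds for discrete adverse events only. As worded, recorded events depend on unblinded attribution, are about zero in no-camera periods whatever the background rate, and cannot show whether the camera causes excess events. The distortion can go either way, and its size cannot be stated from the documents. The figures in the working rest on assumed rates of 2% to 10% per period, assumed attribution of 5% to 20% and full participation of 730 families, and they show only how the rule behaves.

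The consequence is modest. The trial is exploratory, average parental strain is already compared between conditions, and the protocol claims no comparative adverse-event analysis. This is a worthwhile low-cost improvement and does not threaten the main results. The reading rests on the article's single sentence; a fuller protocol that records events in both periods irrespective of cause would settle it.

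**What to change.** In the parent surveys of both 4-week periods, ask about a short pre-listed set of events regardless of judged cause, for example unplanned worried contacts with the ward or acute distress episodes. Record judged relation to the camera as a separate field. Report counts by condition with a within-parent difference and 95% interval. Keep the list of camera-attributed events, but describe it as descriptive device-safety reporting that does not support a comparative conclusion on harm.

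The cost is a few questionnaire items and one sentence of text. This assumes that parents are surveyed in each period, which the cross-over comparison requires although the figure with the timescale is not shown. Two limits remain: the answers are still self-reported without blinding, and events affecting the infant that parents do not know of would not be captured. Hospital incident reports are not proposed, because the documents mention no such source and retrieving them at four sites may not be cheap.

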## Discussion

To our knowledge, this is the first study that comprehensively accompanies and evaluates the use of webcams on multiple NICUs, with regard to parental outcomes and effects on the medical staff. There are already international studies on the use of webcams on NICUs on the topics of additional workload of the nursing staff [13], attitudes towards the cameras of parents, doctors and nursing staff [14, 26], camera usage behaviour [27] and effects of the camera on the length of stay of the premature baby [28]. However, this study examines for the first time primary and secondary outcomes of parents with respect to camera use using validated scales that allow a direct comparison between intervention and control groups. Furthermore, this study benefits from its high number of cases targeted and the evaluation of effects on both parents and physicians as well as nursing staff. In addition, the compilation of practical guidance in the second year provides the opportunity to counteract preconceptions on the parents’ side concerning the camera use and to inform properly about the camera system.

It should be noted, however, that this study is not a clinical study but a health services research study and therefore evaluates the effectiveness not the efficacy. Methodologically, this results in some limitations of the study. A blinding of the intervention and control group is not possible, since the use of the camera is an obvious intervention which cannot be blinded from any of the persons involved. Furthermore, the measured outcomes are mainly patient reported outcomes reported through questionnaires.

Yet this study can be regarded as a pragmatic trial providing necessary evidence to decide whether to promote the use of webcams on NICUs or not and what to consider when implementing them.

## Data Availability

The anonymous datasets generated during the current study may be made available from the corresponding author on reasonable request. Protocol modifications will be communicated to relevant parties such as the publisher of this study protocol or the trial registry. The study manager will oversee the intra-study sharing process. All project members listed in this study protocol will have access to the cleaned anonymous data sets of their respective work packages.

## Abbreviations

GDPR: General Data Protection Regulation
KHG NRW: Hospital Act of North Rhine–Westphalia
MRC: Medical Research Council
NICU: Neonatal intensive care unit
TDM: Total Design Method
WP: Work packages
